## Abstract

**Background and Aims:**

Hearing and vision impairments are prevalent health conditions among older adults, negatively affecting functional ability, mental and social well‐being, quality of life and increasing the likelihood of transition to long‐term care. Sensory impairments are also common comorbidities with dementia, compounding the impact of dementia. Early intervention to optimize sensory function may help older adults stay in their homes longer. The Australian government's ‘Homecare Package’ provides affordable care services to support older adults with complex needs at home; however, there is a lack of support for hearing and vision needs. This trial will investigate whether a sensory support intervention enhances the quality of life and other outcomes for older adults (aged 65 years or older) with diverse cognitive abilities and hearing and/or vision impairments, as well as their care partners.

**Methods:**

This manuscript presents a study protocol for a home‐based sensory support intervention for older adults with hearing and/or vision impairment who receive home care services. A pre‐post study will determine the impact and cost‐effectiveness of a 12‐week intervention. Key outcome measures include health‐related quality of life, sensory and cognitive functional ability, relationships, mental well‐being and health resource utilization. All outcomes will be assessed before the intervention (baseline) and 13‐ and 26‐weeks post‐intervention commencement.

**Conclusion:**

This manuscript describes the protocol for a pre‐post intervention trial. A parallel and complementary process evaluation will be detailed in a separate publication. If effective, the intervention may assist older adults to improve their quality of life and remain living in their own homes. Findings will generate evidence for hearing and vision support as part of home care services.

**Trial registration:** ACTRN12624001167550 retrospectively registered.

## Introduction

1

Hearing and vision impairments are common among community‐dwelling older adults (60 ≥ years) globally, with prevalence rates of 48.3% to 66.5% for hearing loss [1, 2] (defined as > 25dBHTL) and 10.3% to 21.8% for vision loss (defined as visual acuity < 20/40) [3, 4]. These impairments often co‐occur with dementia, which affects 18.7% to 37.1% of community‐dwelling people aged over 65 years worldwide [5, 6]. Sensory impairments can exacerbate dementia‐related declines in cognition, functional, behavior, quality of life, and independence [7, 8]. People with hearing and/or vision impairments or dementia have a greater risk of transitioning to long‐term care facilities due to reduced independence and functional ability [9, 10]. Care partners (family or friends providing support) also experience poorer mental and physical health, especially when supporting individuals with dementia or hearing and/or vision impairment [11, 12].

Hearing and vision interventions improve outcomes for older adults [13, 14], including those with dementia [13], and benefit care partners [15]. Interventions include hearing aids, communication training, spectacles, magnifiers, cataract surgery, and low vision rehabilitation. Early detection and intervention can reduce the risk of severe impairment [16, 17], yet sensory loss is often under‐detected and under‐managed [18]. The gradual onset of hearing and vision impairments often leads older adults to dismiss symptoms as normal aging, which may consequently delay treatment [19, 20]. Dementia complicates detection, as affected individuals may not recognize or communicate hearing or vision difficulties, and care partners may misattribute symptoms to dementia [3, 21].

In Australia, hearing and vision care is predominantly provided by community‐based audiologists and optometrists. Yet, limited engagement with these professionals is a key barrier impacting the health, well‐being, and independence of people receiving aged care services [22]. Barriers include perceived stigma, low awareness of rehabilitation services, accessibility challenges (particularly in rural areas) and out‐of‐pocket costs [23, 24].

Most older adults prefer to ‘age in place’ rather than relocating to long‐term care facilities [22]. Home‐based care reduces costs compared to long‐term care [25], a key priority for governments facing rising care expenses for aging populations [26]. Home care minimizes formal care expenses (accommodation, food, facility maintenance, etc), reduces hospitalizations and leverages informal supports [25]. In 2023‐24, the Australian Government spent AU$21.5 billion on long‐term aged‐care, more than double the AU$11.5 billion allocated to home care [27], with per‐person costs of AU$5,100 for long‐term aged‐care and AU$2,600 for home care [27].

The Australian Government funds home care services for people aged 65 years or older through the ‘Commonwealth Home Support Program’ and ‘Home Care Packages’, addressing basic to complex needs [28]. Services include cleaning, meal preparation, personal care, transport, social support, and nursing care. Usage has quadrupled over the last decade [29], with 24,000 additional packages funded in 2024–2025 [30].

Hearing and vision care have only recently been included in Home Care Packages, so routine checks are rare, and formal referral pathways to hearing or vision care services are lacking. Consequently, hearing and vision impairments frequently go under‐identified and under‐treated, because other care needs are prioritized, and care staff lack expertise in identifying and supporting hearing and vision needs [31]. Effective management and support of hearing and vision health in home care settings requires a multifaceted approach involving older adults, care partners, home care service providers, and the broader care ecosystem [22].

To address the need for integrated hearing and vision services in home care, a home‐delivered sensory support intervention (SSI) was developed to improve outcomes for Australians receiving home care services. Originally based on European research involving people with dementia and their care partners [32], the SSI was adapted through co‐design for broader use in Australia. Co‐design involved older adults with hearing, vision and cognitive impairments, care partners, consumer representatives, and hearing, vision and home care professionals. Tailoring ensured alignment with Australia's aged home care structure, healthcare system, and regulations [33]. The resultant SSI targets older adults with hearing and/or vision impairment, with or without cognitive impairment. This inclusive approach reflects the complex care needs of the ageing population and aims to improve outcomes for all adults receiving home care services.

This paper describes the protocol for a prospective pre‐post‐trial evaluating the SSI across three domains: (i) impact on older adults' quality of life, well‐being, functional ability, and behaviors, (ii) impact on care partners' quality of life, well‐being and relationship quality and (iii) costs and cost‐effectiveness via within‐trial analysis and economic modeling. The research questions to be answered are outlined in Table 1.

**Table 1 hsr271931-tbl-0001:** Research questions.

RQ1	What is the impact of the sensory support intervention on the quality of life of home care recipients and their care partners?
RQ2	What is the impact of the sensory support intervention on home care recipients’ functional ability, visual function, hearing function, and mental and social well‐being?
RQ3	How does the cognitive status of the home care recipient mediate the outcomes of the sensory support intervention, and what are the additional supports required for people with dementia?
RQ4	What is the impact of the sensory support intervention on the mental well‐being of care partners and the quality of their relationship with the home care recipient?
RQ5	What are the costs associated with, and the cost‐effectiveness of, the sensory support intervention compared to usual care?

Abbreviation: RQ, research question.

## Methods

2

The intervention will be delivered over 3 months, with follow‐up at 13‐ and 26‐weeks post‐commencement of the intervention (Figure 1). This 26‐week duration balances participant burden with capturing both short‐ and longer‐term effects. The study protocol follows the Standard Protocol Items: Recommendations for Interventional Trials (SPIRIT) statement (Supplement 1 and 2) [34], and the intervention description, the Template for Intervention Description and Replication (TIDieR) checklist and guide (Supplement 3) [35]. A separate process evaluation protocol [36], outlines a mixed‐methods approach, guided by the UK Medical Research Council framework, to assess implementation fidelity, mechanisms of impact and contextual factors.

**Figure 1 hsr271931-fig-0001:**
[figure not shown]
Flowchart of the study showing participant recruitment, intervention delivery, and follow‐up.

### Ethical Considerations

2.1

Ethical approval was granted by The University of Queensland Human Research Ethics Committee (HE002236; 2024). Participants will receive an information sheet, discuss the study with a researcher, and provide written consent. Accessible materials will be available for participants with dementia or sensory impairments, including plain‐language explanations, large print, audio, and communication support. For deafblind participants, tactile sign language interpreters or other specialist communication methods will be arranged. Proxy consent and participant assent will be obtained where appropriate. If unable to sign, a nominated person may complete the form in the presence of a researcher.

### Setting

2.2

This study will be conducted in the Greater Brisbane metropolitan area (Queensland, Australia) using in‐person and online data collection methods. The intervention will be delivered in participants' homes and clinic settings (audiology and optometry). Data will be collected via online surveys in Qualtrics (Qualtrics XM, Seattle, WA).

### Recruitment

2.4

Eligible participants will be recruited through partner home care providers (e.g., BallyCara, Bolton Clarke, etc.). Recruitment will occur via email, newsletters, social media, community information sessions at home care provider community centers or direct contact by home care provider staff (e.g., case managers, personal care workers, nurses).

### Screening

2.5

Screening will confirm age (≥ 65 years), current receipt of home care services, and presence of hearing and/or vision impairment (Table 2). An otoscopic examination will be conducted before the hearing screening to detect earwax. Individuals with wax will be referred for removal before assessment.

### Intervention Description

2.6

The SSI was adapted from the European SENSE‐Cog SSI, using the UK Medical Research Council's framework for complex interventions [43]. The original intervention was field‐tested and trialed over 5 years [32, 44]. To ensure relevance in Australia [33], the SSI was adapted through iterative co‐design involving home care recipients with hearing and/or vision impairment, care partners, and hearing, vision and home care professionals. This process identified unmet hearing and vision support needs [45], and then adapted the intervention to those needs via a series of interviews and workshops. A Patient and Public Involvement (PPI) group with lived experience of hearing, vision and cognitive impairment reviewed and refined the adapted SSI to ensure suitability for older Australians with hearing and/or vision impairments.

The SSI has been designed to accommodate older adults with single or dual sensory impairment. The intervention includes screening and referral to community clinicians for audiometric or optometric correction, supporting effective assistive device use (e.g., hearing aids), environmental modification (e.g., increasing lighting levels), accessing relevant support services (e.g., low vision services), enhancing communication between the participant and care partner (e.g., communication training), and promoting social inclusion (e.g., connecting with local interest groups). Components are tailored to an individual's hearing and/or vision needs, cognitive and physical ability, current knowledge and skills, access to services, environmental factors, and personal preferences. The intervention comprises eight components (Table 3). Components A, B and C are delivered first, while D to H are delivered flexibly based on participant needs. Key components (A to E) are delivered to all participants, whilst optional components (F to H) are offered based on individual needs and preferences.

**Table 3 hsr271931-tbl-0003:** Description of the sensory support invention components with examples of modifications from co‐design and how the component might be tailored to the individual.

Component	Description (Component Type and Duration)	Example Modifications from Co‐design	Example of Tailoring
A. Identify any vision and hearing concerns and discuss support options	Key Component, duration 60 min The Sensory Therapist discusses hearing and vision concerns and support options with participants, develops a Personal Sensory Plan and arranges hearing and/or vision assessments.	Converted the Personal Sensory Plan questionnaire into an online survey with branching logic to recommend the components that would address needs identified.	For a participant with dual sensory impairment, the Sensory Therapist uses amplification and written materials in large print with high contrast during discussions.
B. Home‐based functional assessment and goal setting	Key Component, duration 120 min A functional assessment will be conducted to ascertain how the home care recipient's cognitive ability and sensory impairments impact a broad range of daily living activities. The assessment outcomes will help shape other components of the sensory support intervention, including referral for support, social inclusion, and supplementary devices. The Sensory Therapist will incorporate the results of the hearing and/or vision assessments and the functional assessment results to help the participants and their study partner set personalized goals using the Bangor Goal Setting Inventory [46]. Goals will be revisited at each visit and the Sensory Therapist will explore facilitators, barriers and resources to the goals and introduce skills and strategies to support progress.	Enhanced the Functional Assessment checklist with representative images to improve accessibility for people with dementia or who are culturally and linguistically diverse.	For participants with cognitive impairment, a pictorial decision tool is used during goal setting to support understanding and choice‐making.
C. Optimization of any vision or hearing impairment	Key Component, duration 60 min An audiologist or optometrist will undertake vision and hearing assessments according to standard procedures as required. The Sensory Therapist helps arrange transport to and from hearing and/or vision appointments with family and/or home care providers. The participant's usual optometrist will provide optometric services. Participants will be reimbursed for the cost of their spectacles up to a $AU 250 amount. Hearing Australia will provide audiological services. Starkey Hearing Technologies and Hearing Australia will provide hearing aids free of charge for the study.	Incorporated a link to Optometry Australia's ‘Find an Optometrist’ feature that allows users to search for dementia‐friendly or low vision specialists in their local area.	For a participant with mobility limitations and no family support, the Sensory Therapist might organize a mobile service to provide a domiciliary visit, with a longer appointment time to accommodate a slower processing speed.
D. Continuous training in correct use of sensory devices	Key Component, duration 60 min The Sensory Therapist will work with participants to enhance adherence and correct usage of the prescribed hearing aids and spectacles. This will include advice given on wearing times, handling, maintenance, cleaning, and storage of devices. The following tests will be administered to monitor participants’ ability to manage their sensory equipment: Hearing Aid Skills and Knowledge test [47] and SENSE‐Cog Glasses Skills and Knowledge test for vision [48].	Hearing aid user and glasses user guides were developed that featured commonly dispensed Australian products.	A participant with arthritis and mild dementia receives simplified, step‐by‐step visual guides for hearing aid insertion and extended hands‐on practice sessions. Training is broken into shorter sessions with frequent repetition, while the study partner is taught to provide daily prompts and assistance.
E. Communication training	Key Component, duration 60 min The Sensory Therapist will work with participants to enhance communication between the home care recipient and their family member/informal caregiver using the SENSE‐cog Communication Manual, which was adapted from existing evidence‐based resources relating to hearing and/or vision impairment and dementia to provide guidance and strategies to enhance communication in different settings. The participants will be provided copies of pre‐existing materials, such as leaflets and video‐based training.	Online Communication Tactic Tool using branching scenarios was developed to provide personalized recommendations.	For a couple where the care recipient has both hearing loss and cognitive impairment, training emphasizes getting attention before speaking, using shorter sentences, and allowing extra processing time. The study partner learns to reduce background noise during conversations and verify understanding without causing frustration.
F. Referral to health and social services	Optional Component, duration 20 min Based on the functional assessments and goals set in Component B, the Sensory Therapist may refer participants to community health or social care services (e.g., psychological services, low vision services, geriatric psychiatry services, falls clinic, etc.)	A list of Australian health and social services, including consumer advocacy groups (e.g., Older Persons Advocacy Network, Vision Australia, Better Hearing Australia, etc.) was created.	A participant experiencing social withdrawal and low mood following vision loss is referred to a low vision support group and counseling services, with the Sensory Therapist facilitating initial contact and providing information in large print format.
G. Fostering social inclusion through hobbies/interests/social groups	Optional Component, duration 20 min In line with the participants’ goals set in component B, the Sensory Therapist will provide information and guidance on opportunities to develop their hobbies and interests or attend local social groups.	Developed a Hobby and Activities decision guide with links to events and activities in Brisbane and surrounds.	A former book club member with vision loss is connected with a local audio book group and provided with information about accessible library services and large‐print book delivery programs that align with their cognitive abilities and reading interests.
H. Environmental modifications and assistive devices	Optional Component, duration 20 min Based on the functional assessment and goals set in component B, the Sensory Therapist may arrange and support the use of environmental modifications (e.g., lighting, increasing contrast, reducing reverberation) or assistive devices (e.g., magnifiers, frequency modulation systems).	Compilation of smartphone accessibility tools (e.g., live captioning) and apps (Be My Eyes) that the Sensory Therapist could recommend to participants was developed.	For a participant with vision impairment and cognitive decline living in a poorly lit home, modifications include installing motion‐sensor lighting in hallways, high‐contrast tape on stairs, and a large‐button amplified telephone. The complexity of devices is matched to the participant's cognitive capacity for independent use.

Delivered over 3 months in 4–6 home‐based sessions (1–2 h each), the intervention is led by a specialist‐trained Sensory Therapist. Training comprises didactic instruction from an audiologist and optometrist, plus an online program covering hearing and vision rehabilitation, communication strategies, assistive technologies, and adaptation to recognize and respond to the needs and challenges of cognitive and dual sensory impairment.

The Sensory Therapist will develop an individualized Personal Sensory Plan (Component A) using bespoke online tools to assess the sensory needs, preferences and functional ability of the participant. The Personal Sensory Plan provides specific recommendations and intervention components to meet those needs. If hearing or vision optimization is needed (i.e., new glasses or hearing aids, or updating existing assistive devices), participants will be referred to an audiologist or optometrist (Component C). Participants then engage in goal‐setting using the Bangor Goal Setting Inventory to prioritize sensory needs [46]. Intervention components are tailored based on hearing and/or vision function, cognitive ability and participant goals. Tailoring is determined collaboratively between the Sensory Therapist, participant and care partner.

All intervention materials are hosted on Canvas (Canvas Instructure, Salt Lake City, UT) an online Learning Management System with accessibility features including black‐on‐white text, high contrast colors, 14‐point font size, text descriptions for images, descriptive hyperlinks, text‐to‐audio functionality and a clear, consistent user interface. The Sensory Therapist will demonstrate platform navigation to participants, who are encouraged to review the information and resources between sessions to consolidate their knowledge and skills. For those without internet access or the skills to use online devices, accessible paper‐based resources will be provided.

### Data Collection

2.7

Quantitative outcomes will be captured at baseline and at 13‐ and 26‐weeks post‐intervention commencement using self‐ or proxy‐report questionnaires (online, paper format, or phone‐administered) (Table 4). Questionnaires take 70 min to complete for home care recipients and 55 min for care partners. For participants living with dementia, accommodations include proxy completion by a care partner, support from a care partner during interviews, and reframing questions to suit communication abilities [49].

**Table 4 hsr271931-tbl-0004:** Overview of the time schedule of intervention and outcome measures.

	Eligibility Screening	Baseline	Intervention Period	Follow‐up		
Timepoint	W‐4–W0	W0	W1–W12	W13	W14–W17	W26
Screening						
Eligibility screening	X					
Informed consent		X				
Intervention						
Sensory Support Intervention						
Assessments						
Home Care Recipient						
Demographic and health status		X				
Sensory and cognitive status		X				
Hearing Screening						
Automated audiometry screening (HearX)	X					
Otoscopy	X					
Vision screening						
Visual acuity screened by Peak Acuity	X					
Cognition screening						
MoCA – HI/VI		X				
FAST Tool	X					
QoL, Function, Well‐being						
HUI3		X		X		X
QOL‐ACC		X		X		X
ASCOT (SCT‐4)		X		X		X
IADLS		X		X		X
RHHIE‐S		X		X		X
NEI VFQ‐25		X		X		X
GAI‐SF		X		X		X
GDS‐5		X		X		X
NPI‐Q		X		X		X
UK Biobank – Social interaction		X		X		X
Care Partner						
Demographic and health status		X				
EQ‐5D‐5L		X		X		X
GAI‐SF		X		X		X
GDS‐5		X		X		X
MoCA		X		X		X
RSS		X		X		X
FCRS		X		X		X
SOS‐HEAR		X		X		X
Resource use						
RUD‐Lite		X		X		X

Abbreviations: ASCOT (SCT‐4), Adult Social Care Outcomes Toolkit 4; EQ‐5D‐5L, European Quality of Life 5‐dimension 5‐level; FAST, Functional Assessment Staging Tool; FCRS, Family Caregiving Role Scale; GAI‐SF, Geriatric Anxiety Inventory Short Form; GDS‐5, Geriatric Depression Scale 5‐item; HUI3, Health Utility Index 3; IADLS, Instrumental Activities of Daily Living Scale; MoCA, HK/VI Montreal Cognitive Assessment Hearing Impaired or Vision Impaired; NEI‐VFQ‐25, National Eye Institute Visual Function Questionnaire 25 item; NPI‐Q, Neuropsychiatric Inventory Questionnaire; QOL‐ACC, Quality of Life Aged Care Consumer; RHHIE‐S, Revised Hearing Handicap Inventory for the Elderly Screening version; RSS, Relationship Satisfaction Scale; RUD‐LITE, Resource Utilization in Dementia Lite; SOS‐HEAR, Significant Other Scale for Hearing Disability; W, week.

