#### Primary Outcomes

2.9.1

Primary outcomes are the home care recipient's self‐rated quality of life, measured using the HUI3 [52] and Quality of Life – Aged Care Consumer (QOL‐ACC) [53] (Table 5). HUI3 is a 40‐item interviewer‐administered (self‐report and proxy) questionnaire that assesses eight health attributes over 1‐week: vision, hearing, speech, ambulation, dexterity, emotion, cognition, and pain [52]. HUI3 has good psychometric properties [52], and has been validated for people with hearing impairment [70], and home care populations [71]. The HUI3 captures quality of life related to hearing and vision and, therefore, may be sensitive to the effect of the intervention in improving health‐related quality of life. The QOL‐ACC, a 6‐item questionnaire assessing mobility, pain, emotional well‐being, independence, social connections, and activities, has been validated for older adults in home care, including those with dementia [53].

**Table 5 hsr271931-tbl-0005:** Battery of Outcome Measures with Scoring Information Administered During Baseline, Week 13, and Week 26.

Construct	Time	Administered by	Information about	Research Question Addressed	Instrument	Description	Scoring & Interpretation
Global Cognitive Functioning	BL	Researcher	HCR Caregiver		Montreal Cognitive Assessment (MoCA) (hearing impaired [54] or vision impaired [55] versions as appropriate	MoCA: 30 items assessing multiple cognitive domains. In the MoCA Hearing Impairment, the items that are presented in spoken format are substituted with suitably adapted written items. Likewise, in the MOCA Vision Impairment, the items that are presented in written format are substituted with adapted verbal items.	The MoCA has a maximum score of 30 points. A final score of 26 and above is considered normal.
	BL		HCR		Functional Assessment Staging Tool (FAST) [37]	The FAST scale is a functional scale designed to evaluate patients with dementia.	The FAST stages dementia from levels 1 to 7, with level 1 representing a normal adult and 7 representing severe dementia.

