Health‐Related Quality of Life	BL, W13, W26	Researcher	HCR	RQ1, RQ5	Health Utilities Index Mark 3 (HUI3) [52]	40‐item questionnaire interviewer‐administered (self‐report and proxy) that is a multi‐attribute utility instrument used to measure health‐related quality of life over a 1‐week period. It evaluates the attributes of vision, hearing, speech, ambulation, dexterity, emotion, cognition, and pain.	HUI3 multi‐attribute utility score scales scores from −0.36 to 1.00, where 0 = dead and negative worse than dead and 1 = perfect health. Differences of 0.03 are clinically important. HUI3 single attribute utility scale scores from 0.00 to 1.00. Differences of 0.05 are clinically important.
	BL, W13, W26	Researcher	HCR	RQ1, RQ5	Quality of Life – Aged Care Consumer (QOL‐ACC) instrument [56]	6‐item questionnaire that incorporates dimensions important and preferred by older people in aged care services. It evaluates mobility, pain, emotional well‐being, independence, social connections and activities.	The QOL‐ACC has a maximum score of 24, where ‘excellent’ quality of life = 22–24, ‘good’ = 19–21, ‘moderate’ = 14–18, ‘poor’ = 8–13, and ‘very poor’ = 0–7.
	BL, W13, W26	Self‐reported	Caregiver	RQ4	European Quality of Life 5‐dimension 5‐level (EQ‐5D‐5L) [57]	5‐item self‐report questionnaire describing five dimensions: mobility, self‐care, usual activities, pain/discomfort, and anxiety/depression	Scores recorded for each test item will be indexed based on the Australian value set. Participant's health related quality of life will be described for each of the five dimensions, and quantified as either; no problems, slight problems, moderate problems, severe problems, or extreme problems
Social Care‐Related Quality of Life	BL, W13, W26	Researcher	HCR	RQ2	Adult Social Care Outcomes Toolkit (SCT4) [58]	9‐item self‐reported questionnaire that is a multi‐attribute utility instrument that captures aspects of social care‐related quality of life.	The SCT4 scores between −0.17 to 1.00, where 0 = dead and negative as worse than dead and 1 = ideal state.
Quality & Quantity of Social Interactions	BL, W13, W26	Researcher	HCR	RQ2	Questions from UK Biobank [59]	3‐item self‐reported questionnaire that assesses social interaction	The Biobank scores for social isolation range from 0 to 3, where 0 = least isolation, 1 = moderate isolation, ≥ 2 = most isolation.

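### The primary outcome is called self-rated, yet proxy reports are allowed for participants with dementia and nothing stated keeps the respondent constant across visits

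*Protocol article*

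**What the plan says.** Section 2.9.1 (Primary Outcomes) opens: "Primary outcomes are the home care recipient's self‐rated quality of life", measured with HUI3 and QOL-ACC. Its next sentence reads: "HUI3 is a 40‐item interviewer‐administered (self‐report and proxy) questionnaire". The HUI3 row of Table 5 agrees: "40‐item questionnaire interviewer‐administered (self‐report and proxy) that is a multi‐attribute utility instrument".

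Section 2.7 (Data Collection) says that outcomes at baseline, 13 weeks and 26 weeks come from "self‐ or proxy‐report questionnaires (online, paper format, or phone‐administered"). It then says, for participants living with dementia only, that "accommodations include proxy completion by a care partner, support from a care partner during interviews, and reframing questions to suit communication abilities".

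Eligibility (section 2.3) runs from normal cognition to moderately advanced dementia, FAST stage 6, and a care partner is optional. Section 2.10.1 (Impact Analysis) lists as covariates demographics, health, cognitive and sensory function, sex, gender and sensory support use. The only sensitivity analysis it names excludes participants with major acute events. The Discussion acknowledges that there is no control group.

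**The concern.** Who gives the rating is part of what the outcome is. The article defines the primary outcome as self-rated and also admits a proxy rating of the same instrument. This is a conflict in the printed text, not a detail left to an analysis plan.

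The design makes it matter. With no control arm, the within-person change is the whole estimate. If a participant answers for themselves at one visit and a care partner answers at another, the gap between the two raters is added to that person's change, and no comparison group shares it. The switch can run either way. Decline could move someone from self to proxy, and better hearing, vision or communication could move someone from proxy to self.

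Adjusting for cognitive function does not solve this. Table 4 schedules the recipient's MoCA at baseline and FAST at screening, and neither can absorb a later change of rater. RQ3 asks how cognitive status bears on the outcomes, and it is the more exposed question because the proxy accommodation is confined to participants with dementia. If respondent type is not recorded at the visit, it cannot be recovered reliably later.

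**Working it through.** **The plan's own figure.** Section 2.3 gives d = 0.3, 80% power, two-sided 5%, a correlation of 0.6 and 20% attrition. For a paired comparison, n = (1.960 + 0.842)² × 2(1 − 0.6) / 0.3² = 7.849 × 0.8 / 0.09 = 69.8, so 70 completers. Dividing by 0.8, 69.8 / 0.8 = 87.2, which matches the stated 87. So d = 0.3 is in units of the cross-sectional SD, and the bias below is on the same scale.

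**Formula.** Bias in mean change = share of the sample that switches × self-proxy gap in SD. Share that switches = share with dementia × proportion of those who switch.

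**Inputs.**
- Share with dementia: the article gives none for this trial. The Introduction's background range for community-dwelling people over 65, 18.7-37.1%, is borrowed. A home-care sample may differ.
- Proportion of those with dementia who switch: 10-20%, assumed.
- Self-proxy gap: 0.3-0.5 SD in absolute size, assumed, sign unknown.

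**Share of the whole sample switching.** Low: 0.187 × 0.10 = 0.0187. High: 0.371 × 0.20 = 0.0742. That is about 2-7%, or 1 to 5 of 70 completers.

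**Bias in the primary change.**

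| Dementia share | Switch among them | Gap 0.3 SD | Gap 0.5 SD |
|---|---|---|---|
| 18.7% | 10% | 0.006 SD (1.9% of d) | 0.009 SD (3.1%) |
| 18.7% | 20% | 0.011 SD (3.7%) | 0.019 SD (6.2%) |
| 37.1% | 10% | 0.011 SD (3.7%) | 0.019 SD (6.2%) |
| 37.1% | 20% | 0.022 SD (7.4%) | 0.037 SD (12.4%) |

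**Effect on the test at the worst corner.** Switch share s = 0.0742, gap g = 0.5, 70 completers, and the 5% level of the sample size statement. Variance of change = 2(1 − 0.6) + s(1 − s)g² = 0.8 + 0.0742 × 0.9258 × 0.25 = 0.817. SE = √(0.817 / 70) = 0.108. Bias / SE = 0.0371 / 0.108 = 0.34. The true type I error is then about 0.064 rather than 0.05. If a switch lowers the follow-up rating, power for d = 0.3 is Φ((0.3 − 0.0371) / 0.108 − 1.96) = 0.68 rather than 0.80. If it raises the rating, apparent power is 0.88. At the mildest corner the type I error stays at 0.050 and power is 0.79-0.82.

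**RQ3.** Within participants with dementia the bias is not diluted: 0.10 × 0.3 = 0.03 SD to 0.20 × 0.5 = 0.10 SD. If participants without dementia do not switch, a contrast by dementia status carries that full amount.

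**The case against.** Four counter-arguments have force.

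**Scope.** Proxy completion is offered only to participants living with dementia, and only those with a care partner can use it. The broader phrase about self- or proxy-report covers the whole battery, which includes the NPI-Q, a proxy instrument by design. This stands. A reader might infer that 10-20% of the whole sample could switch, giving a bias of 10-33% of d = 0.3. The documents do not support that. At a dementia share of 37.1% it would need 27-54% of participants with dementia to change respondent, and at 18.7% it would need 53-107%, the top of which is impossible.

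**Likelihood.** FAST stage 6 is only the upper limit for entry. Someone who cannot self-report at baseline would have a proxy from the start and would not switch. The sample size rests on the 13-week contrast, which leaves less time for decline than 26 weeks. So the documents show that switching is possible, not that it is likely.

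**Mode.** A reader might also see a conflict between interviewer administration of HUI3 and the online, paper or phone options. Table 5 is specific to each instrument and lists the researcher for HUI3 and QOL-ACC. The mode list in section 2.7 describes the whole battery, including forms that care partners complete themselves. The two can largely be read together.

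**Omission.** The article condenses a fuller protocol that may hold a same-respondent rule, and nothing printed says that self and proxy responses will be pooled without distinction. That is fair, so pooling is not asserted here. It does not remove the conflict over who rates the primary outcome, nor the fact that the covariates and sensitivity analysis that are printed pass over respondent.

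**Conclusion.** The point holds in a limited form. The article gives two incompatible descriptions of who rates the primary outcome. As printed, nothing keeps the respondent constant for participants with dementia or accounts for a change of respondent. Any such change enters the uncontrolled pre-post estimate and the RQ3 comparison.

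The likely effect on the primary estimate is modest: about 0.006-0.04 SD, 2-12% of d = 0.3, in either direction. This rests on two assumed inputs (the switching proportion and the self-proxy gap) and one borrowed input (the dementia share). A sample with more dementia or more switching would push it higher. The sample size of 87 is unaffected. The change is worth making because it costs little and the information is lost if it is not recorded at the time.

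**What to change.** - Describe the primary outcome in section 2.9.1 as self- or proxy-rated, so that it agrees with section 2.7 and Table 5.
- Set the respondent for HUI3 and QOL-ACC at baseline for each participant and keep the same respondent at weeks 13 and 26 where possible.
- Record respondent type (self or proxy) at every visit.
- Keep all participants in the primary model. Add two sensitivity analyses: one restricted to participants whose respondent did not change, and one restricted to self-report.

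The primary contrast should not be restricted to same-respondent pairs. That would exclude people on a post-baseline event tied to cognitive decline, which in an uncontrolled trial could itself favour the intervention.

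The cost is one data-collection instruction, one recorded field and a little extra analysis. This is a cheap improvement.
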